### **8.2.2.3 Secondary Analysis of Volume measurements**

A secondary analysis of the primary outcome measure will be based on a multi-level modelling approach to investigate the relationship between any change in tumour volume and randomised treatment accounting for the three measurements within each tumour as well as multiple tumours within individual patients and multiple measures at baseline and 12 weeks. Random effects multilevel models will account for the nested tumour measurements within both time points and patients, and account for baseline volume measurement and randomised treatment group as covariates. Confidence intervals will be reported.

A repeated measures analysis will look at the mean volume over time at baseline, 4 weeks and 12 weeks accounting for multiple tumours within individual patients including randomised treatment group as a covariate.

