### 3.2 Randomisation: Phase 2a only

Randomisation is at the per patient level randomising active and placebo treatments to left or right sided application. There are no stratification factors.

Four or five tumours matched for size will be selected on each side of the patient. Each tumour will be assigned a number to facilitate assessments and then each side of the patient will be allocated randomly to receive either active ointment or placebo ointment.

The number of tumours and unique number of patients recruited will be reported. The number of tumours in each of active and placebo group will be reported.

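### SAP 8.2.2.3 leaves the volume models under-specified: baseline is among the outcome times, no treatment-by-time term or 12-week contrast is named, and the randomised side has no random effect

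*Combined protocol and SAP*

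**What the plan says.** SAP 8.2.2.3 describes two secondary models for tumour volume in Phase 2a.

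- **Multilevel model.** Its aim is to "investigate the relationship between any change in tumour volume and randomised treatment". It allows for three readings per tumour and for "multiple tumours within individual patients and multiple measures at baseline and 12 weeks". On structure it says: "Random effects multilevel models will account for the nested tumour measurements within both time points and patients". The models also "account for baseline volume measurement and randomised treatment group as covariates".
- **Repeated measures model.** It will "look at the mean volume over time at baseline, 4 weeks and 12 weeks accounting for multiple tumours within individual patients". Treatment enters this model, too, as a covariate.

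Neither description mentions a treatment-by-time interaction, a contrast at 12 weeks, or a level for side of the body.

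On allocation, SAP 3.2 states: "Randomisation is at the per patient level randomising active and placebo treatments to left or right sided application". Four or five size-matched tumours are chosen per side, and then "each side of the patient will be allocated randomly to receive either active ointment or placebo ointment". Protocol section 11 agrees. SAP 8.1.2 (primary outcome, Phase 2a) places the first volume measurement before randomisation.

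SAP 8.2.3.1 applies the methods of 8.2.2 to surface area and height as well.

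**The concern.** Baseline volume is measured before allocation, so the expected active-placebo difference at that time is zero. If baseline is one of the outcome times and treatment enters only as a main effect, the treatment coefficient is an average over times that includes this zero. It then does not estimate the 12-week effect.

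The second issue is the unit of randomisation. Each patient contributes one active side and one placebo side, so a trial of 15 to 20 patients has 15 to 20 randomised pairs. A model with patient and tumour levels but no side level treats the four or five tumours on a side as independent replicates of treatment. Anything shared by one side (how well it was treated from its own jar, or a patient-specific response to the drug) then appears as extra precision.

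The rest of the SAP reports volume change and response arm by arm. These models are where an active-versus-placebo difference is estimated directly and where clustering is addressed. A diluted coefficient or an interval that is too narrow would therefore weaken the planned reading of secondary outcome (a), change in tumour volume.

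**Working it through.** **Plan's own figure.** The documents give no figure for the volume models. The only design calculation is the Fleming-A'Hern one in protocol 14.2 (75 active-arm tumours, 5% against 15%). It reproduces with 8 or more responses: exact binomial type I error 0.0336 and type II error 1 − 0.8918 = 0.1082, against the stated 3.4% and 10.8%. It has no bearing on this point.

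**Inputs from the documents.** Outcome times and covariates (SAP 8.2.2.3); baseline before randomisation (SAP 8.1.2); side as the randomised unit, 4 or 5 tumours per side (SAP 3.2); 150 tumours in 15-20 patients (SAP 1.1).

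**Assumed, because not given.** The week-4 effect as a share of the week-12 effect (range 0 to 1). The side-level ICC, meaning the share of variance left after the patient effect that is common to tumours on one side (range 0 to 0.3).

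**Step 1: what the treatment coefficient estimates.** With balanced data, a treatment main effect equals the mean of the treatment differences at the outcome times. Write d4 and d12 for the true differences; the baseline difference is 0.

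- Two-time model, volume as outcome: (0 + d12)/2, a share of 0.50. Mixed-model simulation gave 0.50 to 0.51.
- Same model, change from baseline as outcome: d12, a share of 1.0.
- Three-time model: (0 + d4 + d12)/3, so the share is (d4/d12 + 1)/3.

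| Week-4 effect assumed | d4/d12 | Share of 12-week effect | Simulated |
|---|---|---|---|
| none yet | 0 | 0.33 | 0.29 |
| linear in time | 4/12 | 0.44 | 0.41 |
| half reached | 0.5 | 0.50 | 0.55 |
| fully reached | 1 | 0.67 | 0.67 |

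The simulations used 15 patients with 5 tumours per side and only 15 runs per scenario. They check the algebra and do not replace it. On the same data, a treatment-by-time model read at week 12, or week-12 volume adjusted for baseline, returned 1.00 to 1.03 of the true effect.

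**Step 2: what omitting side does to the interval.** Take P = 15 patients, m = 5 tumours per side, side-level ICC ρ, and variance 1 after the patient effect.

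- True variance of the active-placebo difference: (2/(Pm)) × (1 + (m − 1)ρ) = (2/75)(1 + 4ρ).
- Variance reported by a patient-plus-treatment model: (2/75) × s². It has 2Pm − P − 1 = 134 degrees of freedom, and the expected s² is [120(1 − ρ) + 14(1 + 4ρ)]/134.
- At ρ = 0.1: true factor 1.40, expected s² = (108 + 19.6)/134 = 0.952, ratio 1.47. The true standard error is √1.47 = 1.21 times the reported one.
- At ρ = 0.2: 1.80 against (96 + 25.2)/134 = 0.904, ratio 1.99, standard error 1.41 times the reported one.

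Simulated two-sided error at nominal 5% (4,000 trials per value):

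| Side-level ICC (assumed) | Side omitted | Paired side means |
|---|---|---|
| 0 | 5.2% | 5.5% |
| 0.05 | 6.8% | 4.8% |
| 0.1 | 10.9% | 5.3% |
| 0.2 | 16.8% | 4.9% |
| 0.3 | 21.8% | 4.9% |

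For intervals, 100% minus these figures gives the coverage of a nominal 95% CI: about 89% at ICC 0.1 and 83% at 0.2 with side omitted.

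**The case against.** The strongest reply is that the SAP is silent on these details, not wrong about them. It gives no model equation and does not exclude an interaction. The multilevel model is said to concern change in volume; a change outcome with baseline as covariate is ordinary analysis of covariance and has no dilution. That reading is open, so it cannot be said that the SAP commits to a main effect only or that it halves the treatment effect. It fits poorly, however, with the nesting of measurements in time points in the same paragraph, and it is not available for the repeated measures model, whose outcome is mean volume at three times including baseline.

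Other replies also stand in part:

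- Baseline among the outcomes is not a fault in itself. Longitudinal models that constrain the baseline means to be equal do this properly, but they need the treatment-by-time term.
- A reader might infer that repeated measures on the same tumour are ignored in the second model. Calling it a repeated measures analysis ordinarily implies a tumour level, so the text does not support that; the level should simply be named.
- The side-level ICC is unknown and could be zero, in which case nothing is lost. Size matching across sides may help. No significance test is planned, so the relevant consequence is interval coverage.
- A reader might fear that a real effect would be hidden. SAP 8.2.2.1 and 8.2.2.2 report 12-week percentage change and response by arm with 95% CIs, so undiluted arm-level results will sit beside any model coefficient.

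**Conclusion.** The point holds as under-specification with a measurable cost if the text is followed literally. The coefficient would be about 0.50 of the 12-week effect in the two-time model with volume as outcome (1.0 with change as outcome). In the three-time model it would be 0.33 to 0.67, depending on the unstated week-4 effect. That two implementations of one paragraph can differ by a factor of two is itself a weakness in a pre-specified plan.

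The missing side term leaves the estimate alone. It narrows intervals only to the extent that same-side tumours correlate beyond the patient effect: nominal 5% error is about 5%, 7%, 11%, 17% and 22% at assumed ICCs of 0, 0.05, 0.1, 0.2 and 0.3, with 15 patients and 5 tumours per side.

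The reach is limited to the secondary, exploratory volume models and, through SAP 8.2.3.1, surface area and height. It might be inferred that the go/no-go decision is compromised. The documents do not support that: the primary analysis is the 12-week response proportion (SAP 8.2.2.2), and the decision rests predominantly on the response rate and the critical number of responses (SAP 8.4). Neither uses these models. This should be fixed, but it is not a condition for the trial to proceed.

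**What to change.** Amend SAP 8.2.2.3 to state the following.

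1. **Outcome and baseline.** For the multilevel model, use week-12 volume (or change from baseline) as outcome with baseline volume as covariate. For the repeated measures model, use weeks 4 and 12 as outcomes with baseline as covariate, or all three times with baseline means constrained equal between treatments. In either case include treatment-by-time.
2. **Estimate.** Report the week-12 active-versus-placebo contrast with its 95% CI.
3. **Random effects.** Include patient, side within patient, and tumour. The reading level can be kept where the three readings are modelled separately.

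A log scale, reporting as a ratio and the choice of degrees-of-freedom method are optional. A log scale would need a stated rule for tumours that disappear, since their volume is zero.

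The cost is SAP wording. Data collection and software do not change. Intervals may be wider, because they will reflect 15 to 20 randomised pairs of sides rather than 150 tumours.

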## **8.2.3 Analysis of secondary outcome measures**

Secondary outcomes will be analysed using the Phase 1b and phase 2a trial sets separately as Cohort 1 and cohort 2.

### **8.2.3.1 Other Tumour measures**

Tumour measurements of surface area and height will be analysed as described for the primary outcome in 8.2.2 above.

Expression of targets of TRK signalling in tumour biopsies will be analysed and reported graphically.

### **8.2.3.2 QoL Measures**

The Patient Treatment Questionnaire will be analysed descriptively reporting the number of patients answering each response level in each question and reported as a proportion of the treatment set. In Phase 2a the additional question 5 will be reported as the proportion of patients who were able to correctly identify which side had been allocated the treatment ointment. Comments left in the text box will be listed.

Health states determined by the EQ-5D will be reported as numbers (%) of patients in the trial set responding to each dimension. The median (IQR) score for each of the 5 dimensions reported for the Phase 1b trial set and the Phase 2a trial set. The EQ-5D VAS score will be reported as mean and standard deviation (SD).

The mean and SD of the DLQI score will be reported and number and percentage of participants in each scoring band as well as median score and IQR. The analysis set is the trial set.

### 8.2.3.3 Pain measures

Relating to Phase 2a is the Pain Assessment form. The results will be reported descriptively, separately for Phase 2a active and placebo sets. Number of painful tumours per patient at baseline 4 and 12 weeks, the number of tumours becoming painful during treatment, the number of tumours where pain is reduced during treatment and the number of tumours where pain increases during treatment. Nature of pain will be reported as the number of tumours listed under each pain type and the pain scale will be reported as median range and IQR.

There will be no significance testing.

## 8.3 Additional Analyses

According to the WHO-RECIST criteria, a 30% reduction in volume is sufficient to classify a “response” to treatment in oncology. In this trial we use this criteria as a bench mark when determining a response in this patient population. As such a further outcome is to consider and confirm a definition of “response” to treatment in this group of patients. We will consider how many tumours are responders, stable or progressive disease at different levels of “partial response”. We will report the number of tumours who would be classified as responders for lower levels of reduction in tumour volume at both 4 weeks and 12 weeks. Response rates in the trial set will be presented in tabular form for alternative definitions, based on -5% and - 10% changes in the RECIST definition (Appendix 4).

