| Primary outcome:       | The proportion of tumours responding to treatment by 12 weeks.                                                                                                                                                                                                                                                                                                                                                                                                                                                                                                                                                                                                                                                                                                                                                                                                                                   |
| Secondary outcomes:    | 

a. Change in tumour volume from baseline (pre-randomisation) to 12 weeks

b. Adverse events within a planned 12-week treatment period

c. Compliance including reasons for non-compliance

d. Confirmation of the definition of response (currently according to WHO RECIST criteria where response is defined as >30% reduction in tumour volume, this will be used as a benchmark).

e. Expression of targets of TRK signalling in tumour biopsies as determined by QPCR and immunohistochemistry.

f. Patient reported quality of life using patient reported QoL tools (EQ5D, DLQI)

g. Assessment of acceptability of trial treatment according to patient treatment questionnaire (Appendix B).

h. Patient reported pain using the Patient Pain Assessment Form at 0, 4 and 12 weeks.

 |

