### 8.2.1 Cohort 2: Outcome measures:

|                          |                                                                                                                             |
|--------------------------|-----------------------------------------------------------------------------------------------------------------------------|
| Primary outcome measure: | The proportion of tumours responding to treatment by 12 weeks in both actively treated lesions and placebo treated lesions. |
|--------------------------|-----------------------------------------------------------------------------------------------------------------------------|

|                             |                                                                                                                                                                                                               |
|-----------------------------|---------------------------------------------------------------------------------------------------------------------------------------------------------------------------------------------------------------|
| Secondary outcome measures: | a. Change in tumour volume from baseline (pre-randomisation) to 12 weeks assessed by a tumour volume measuring device, (Skvara et al. )
b. Adverse events within a planned 12 week treatment period |
|-----------------------------|---------------------------------------------------------------------------------------------------------------------------------------------------------------------------------------------------------------|

- c. Compliance as reported in the patient diary, including reasons for non-compliance
- d. Confirmation of the definition of response (currently according to WHO RECIST criteria where response is defined as >30% reduction in tumour volume, this will be used as a benchmark).
- e. Expression of targets of TRK signalling in tumour biopsies as determined by QPCR and immunohistochemistry.
- f. Patient reported QoL tools (EQ5D, DLQI)
- g. Assessment of acceptability of trial treatment according to patient treatment questionnaire (Appendix B).
- h. Patient reported pain using the Patient Pain Assessment Form at 0, 4 and 12 weeks.

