### **8.3 Cohort 2 Inclusion criteria:**

- Males and females age 18 years and older
- For women of child bearing age: a negative pregnancy test is required prior to study entry, and on completion of trial treatment. The patient must be using an adequate contraception method (as defined in section 10.4) and agree to continue using this throughout the trial and for at least 2 weeks after stopping the trail medication
- Sexually active men must agree to use barrier forms of contraception
- Patients from genotyped pedigrees with known *CYLD* mutations, or if they have a clinical phenotype compatible with this diagnosis

- Patients will optimally have 8-10 eligible tumours
- Eligible tumours will be ideally less than 1 cm in diameter and no more than 2 cm in diameter at the base
- Eligible tumours must be spaced at least 1 cm apart from other eligible tumours to avoid cross-contamination
- The recruiting clinician must be confident that the patient understands the consent process and has the capacity and willingness to provide fully informed consent for participation in the trial
- Patients who have completed cohort 1 without adverse reaction and after completing a minimum 2 week treatment free washout period

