#### **8.1.2 Primary Outcome – Phase 2a**

The primary outcome measure is the proportion of tumours responding to treatment by 12 weeks. According to WHO-RECIST criteria, a reduction in 30% volume would be sufficient to classify a "response" to treatment in oncology. In Phase 2a we will use this criteria as a benchmark when determining a response in this patient population at 12 weeks.

Tumour volume will be measured on the predetermined identified tumours in each patient prior to randomisation and measured again and recorded on the same tumours at 4 and 12 weeks. We will have measures of surface area, height and volume taken 3 times at each visit for each tumour. The mean of each set of 3 measurements will be used to determine the percentage change in volume for each tumour to be able to classify tumours as having a response to treatment or not at each time point (Appendix 3).

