## 8.4 Decision Criteria

The decision to progress from Phase 1b to Phase 2a will be based on the number of severe skin reactions reported, with guidance and recommendations from the trial DMC, as reported in the statistics section of the trial protocol and trial master file.

Decision criteria at the end of Phase 2a are predominantly based on the response rate and critical number of responses observed in the treatment group, according to the Fleming A’Hern design. Tumours receiving placebo treatment are not expected to respond to treatment. Using Fleming A’Herns early phase methodology (Fleming 1982, Ahern 2001) any response on the experimental treatment <5% would not indicate a treatment worthy of further investigation. The justification to investigate CT327 further is based on observing a minimum number of responses referred to as the critical number as specified in the document entitled “Critical Number” which is located in the Statistical Trial Master File.

The benchmark for the definition of ‘response’ was set as 30% reduction in tumour volume given the WHO RECIST oncology criteria. As specified in the protocol, consideration will be given to shifts in this criteria, to smaller reductions in volume, to observe the impact on the response rate and Fleming A’Hern critical number in the treatment group, as outlined in 8.3 above. The reasoning for this exploratory analyses in this early phase clinical trial is to allow further investigation of a biologically interesting treatment which may have not hit a statistical boundary. The conclusions from the trial will be discussed with the DMC and reported with their independent guidance and recommendations.

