### Additional Analysis

| Reduction in tumour volume | Complete Response | Partial Response | TOTAL RESPONSE | Stable Disease | Disease Progression | Not applicable | Total |
|----------------------------|-------------------|------------------|----------------|----------------|---------------------|----------------|-------|
| ≥ 20%                      | N (%)             |                  |                |                |                     |                |       |
| ≥ 25%                      |                   |                  |                |                |                     |                |       |
| ≥ 30% (RECIST)             |                   |                  |                |                |                     |                |       |
| ≥ 35%                      |                   |                  |                |                |                     |                |       |
| ≥ 40%                      |                   |                  |                |                |                     |                |       |

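### The response definition is to be confirmed by counting responders at shifted cut-offs, with no placebo rate named at those cut-offs and no planned report of reading error

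*Combined protocol and SAP*

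**What the plan says.** Protocol section 4.2 and the Cohort 2 outcome table list as a secondary outcome "Confirmation of the definition of response (currently according to WHO RECIST criteria where response is defined as >30% reduction in tumour volume", with 30% serving as a benchmark. SAP 8.3 takes this up as a further outcome and plans two things: "We will report the number of tumours who would be classified as responders for lower levels of reduction in tumour volume", at 4 and 12 weeks, and "Response rates in the trial set will be presented in tabular form for alternative definitions, based on -5% and - 10% changes in the RECIST definition".

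The shell table in SAP Appendix 4 has rows at 20, 25, 30, 35 and 40%. Its columns are "Complete Response | Partial Response | TOTAL RESPONSE | Stable Disease | Disease Progression | Not applicable | Total". There is no arm column and no separate layout for the two time points.

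SAP 8.4 says that smaller reductions will be considered "to observe the impact on the response rate and Fleming A’Hern critical number in the treatment group, as outlined in 8.3 above". Its stated reason is to allow further investigation of a biologically interesting treatment that may not have reached a statistical boundary.

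On measurement, SAP 8.1.2 states: "We will have measures of surface area, height and volume taken 3 times at each visit for each tumour". The mean of the three readings classifies response. Protocol 13.2 describes the imaging system as validated and reproducible but gives no repeatability figure. On size, the Cohort 2 inclusion criteria say: "Eligible tumours will be ideally less than 1 cm in diameter and no more than 2 cm in diameter at the base". They set no lower limit.

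**The concern.** A cut-off is supported when falls of that size are uncommon in tumours without active drug and exceed what re-measurement alone produces. A table of counts shows neither. Lowering the cut-off can only keep or add responders, whatever the cause, and no text says how the counts would lead to 30% being kept or changed.

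This would be a small matter if the table were purely descriptive. SAP 8.4, however, lets the smaller cut-offs enter the discussion of whether to investigate CT327 further, and it names the treatment group alone. Those are the cut-offs most exposed to measurement error. At stake are a stated outcome, which a later trial would rely on for its endpoint, and the reading of a result that falls short at 30% but passes at 20% or 25%.

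**Working it through.** **1. The plan's own design figures.** Inputs from protocol 14.2: 75 active tumours, p0 = 5%, p1 = 15%, type I error 3.4%, type II error 10.8%. Let X be binomial(75, p) and r the critical number.

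- r = 8: P(X ≥ 8 | 0.05) = 0.0336, and 1 − P(X ≥ 8 | 0.15) = 1 − 0.8918 = 0.108. Both stated figures are reproduced.
- r = 7 gives 8.1% and 5.4%; r = 9 gives 1.2% and 18.9%. Neither matches.

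The implied critical number is therefore 8 of 75. The SAP keeps the actual number in a separate file, so 8 is inferred.

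**2. What a count without arms can show.** Suppose 15 of 150 tumours respond at some cut-off (10%). That fits 15/75 against 0/75 (20% v 0%) and equally 8/75 against 7/75 (10.7% v 9.3%).

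**3. How often unchanged tumours would cross a cut-off.** The documents give no error figure, so s below is an assumption. Let log volume vary from visit to visit with SD s and no true change. The log ratio of week 12 to baseline then has SD s√2, and the chance of an apparent fall of at least k is Φ( ln(1 − k) / (s√2) ).

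For example, with s = 0.15:
- k = 30%: ln 0.7 = −0.357; −0.357/0.212 = −1.68; Φ = 4.6%.
- k = 20%: ln 0.8 = −0.223; −0.223/0.212 = −1.05; Φ = 15%.

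The chance of reaching 8 of 75 follows from the binomial, treating tumours as independent.

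| Assumed s | False falls ≥30% | Chance of ≥8/75 | False falls ≥20% | Chance of ≥8/75 |
|---|---|---|---|---|
| 10% | 0.6% | <0.1% | 6% | 7% |
| 15% | 4.6% | 2% | 15% | 88% |
| 20% | 10% | 52% | 22% | >99% |

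**4. Reading error that averages out.** If the three readings have independent lognormal errors with a CV of 20% each (again assumed), simulation of the ratio of two three-reading means gives 1.4% false falls at 30% and 8.6% at 20%. The chance of at least 8 of 75 is then below 0.1% at the 30% cut-off. At the 20% cut-off it is P(X ≥ 8 | 75, 0.0856), about 31%.

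**5. What is collected.** If complete, 150 tumours × 3 visits × 3 readings = 1,350 readings, with 150 × 3 × 2 = 900 within-set degrees of freedom for repeatability, plus about 75 placebo tumours.

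**6. What the plan reports.**

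| Quantity | Planned? |
|---|---|
| Response at 30%, by arm, with 95% CI | Yes: SAP 8.2.2.2, Appendix 3 |
| Response at other cut-offs, active | Yes: SAP 8.4 with 8.3 |
| Response at other cut-offs, placebo | Not named in the SAP |
| Mean % change by arm and by baseline-diameter quartile | Yes: SAP 8.2.2.1, Appendix 3 |
| Three readings in a multilevel model | Yes: SAP 8.2.2.3 |
| Reading-level variance or smallest detectable change | Not stated |
| Text linking any of these to keeping or changing 30% | None |

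**The case against.** The strongest reply is that the rest of the plan supplies much of what SAP 8.3 lacks. Protocol 14.1 says that Cohort 2 descriptive data are presented by treatment group, and Appendix 4 is only an empty shell, so arm columns could be added without departing from the protocol. The placebo rate at 30%, with its interval, is direct evidence of how often such a fall occurs without active drug, between-visit error included. The triplicates enter the multilevel model, from which a reading-level variance can be taken. The effect of baseline size is examined by diameter quartile and arm. The trial is openly exploratory, and the conclusions go to the DMC.

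All of this stands, and it limits the point. A reader might infer that the plan as a whole cannot show whether a 30% fall exceeds error, or that the triplicates go unused. The documents support neither. What remains is that no placebo rate is named at the alternative cut-offs, SAP 8.4 names only the treatment group when it uses them, and the reading-level spread is not promised as a result.

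A reader might also want 30% of volume restated as a change in diameter, or a fixed test for confirming 30%. The first assumes that tumours shrink without changing shape; the documents define response by volume and analyse height and surface area separately. The second would rest on a weak limit: the 5th percentile of about 75 placebo tumours is roughly the fourth-lowest value (0.05 × 75 = 3.75), before allowing for clustering in 15-20 patients.

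**Conclusion.** The point holds for SAP 8.3, Appendix 4 and the use made of them in SAP 8.4. As planned, the counts cannot show on their own whether a smaller cut-off captures shrinkage or noise, and the comparison that would help is not named.

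The size is conditional. Under the assumed SDs of 10% to 20%, false falls range from 0.6% to 10% at the 30% cut-off and from 6% to 22% at the 20% cut-off. Moving from 30% to 20% at an SD of 15% takes the chance of reaching 8 of 75 on noise alone from 2% to 88%. These figures assume lognormal error, no true change, independent tumours and an inferred critical number of 8. The real error could be smaller and the problem slight; the documents do not say. They also give no figure for how error depends on tumour size.

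The change is worth making but not critical: the outcome is secondary and exploratory, yet it feeds the decision to go on.

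**What to change.** Amend SAP 8.3, 8.4 and Appendix 4.

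1. Split Appendix 4 into Active and Placebo columns at every cut-off, at both 4 and 12 weeks. In SAP 8.4, read any shifted cut-off in the active arm against the placebo rate at the same cut-off.
2. From the triplicate readings, report the within-visit SD or CV and the smallest detectable percentage change, overall and by baseline size. Note that these capture within-visit error only.
3. Report the placebo-side distribution of 12-week percentage change, allowing for clustering within patient. Note that it mixes between-visit error with natural change and any vehicle effect.
4. State that items 2 and 3 will be used descriptively when discussing whether to keep or change 30%.

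The cost is some SAP wording and a few extra tables from data already collected. The drawback is that the 30% cut-off, or the lower ones, may be shown to lie within measurement error.
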